#### Implementing CAMS and adherence training

Recruitment of project therapists began in the spring of 2014; the project is continuously including and training new therapists when needed. We have trained CAMS therapists by applying two different models. Initially, we offered a traditional workshop training program, but later experienced the need for extended training possibilities. Flexibility is important, and we continuously need to be able to offer training due to natural therapist turnover in staff (see Table 2 for a summarization of learning steps in the two models).

**Table 2 Tab2:** CAMS training

	Teaching philosophy and strategies	Skills training, role play	Shared literature	3 videotaped supervised therapies	Acceptable scores on the CAMS Rating Scale
2 days traditional workshop	✓	✓	✓	✓	✓
1 day e-learning and 1 day workshop	✓	✓	✓	✓	✓

The two first groups were trained at a 2-day introductory workshop in the CAMS theory, philosophy, and strategies by a Danish clinical psychologist and approved CAMS trainer. The workshop emphasized and facilitated in vivo training of the CAMS strategies through group work where the participants joined up in pairs and exercised new skills in role play. Other therapists who joined the project later have instead followed the online training program in CAMS with American experts. First, these therapists completed the e-learning course (which requires approximately 1 work day) in a self-paced manner and then met in a 1-day workshop with other e-learners and a CAMS supervisor. During the workshop, the CAMS philosophy and strategies were reviewed, and the group practiced CAMS strategies using role playing and interview techniques. In addition to a selection of CAMS-related teaching material, all trainees have received a copy of the CAMS treatment manual as well as Jobes’ book *Managing Suicidal Risk: A Collaborative Approach* [15]*.*

To be approved as a project therapist in the CAMS group, the therapists must conduct three videotaped training therapy sessions following the introductory training. All training therapies were rated by project staff according to the CAMS Rating Scale (CRS), which contains 14 statements covering three main areas of competency: “therapeutic philosophy,” “session framework,” and “overall rating.” Each statement is scored on a 7-point Likert scale. In order to qualify, a mean score of 3 or “satisfactory” (3 or more) was required on the CRS. Of 30 potentially eligible therapists who completed CAMS training, 14 therapists completed the adherence training. Those who completed adherence training met the requirements on the CRS to be approved as a CAMS therapist. Nonetheless, currently only 9 are actively involved and treat recruited patients in the study. After adherence approval, the CAMS therapists are offered supervision from the first author (WR) upon request.

#### TAU intervention

All patients included in the trial receive treatment within specialized care in our clinic. The TAU intervention consists of psychotherapy from diverse theoretical orientations such as psychodynamic, cognitive, or eclectic orientations, combined with psychopharmacological treatment as needed; these treatments are not manualized. A typical outpatient practice is weekly sessions with a duration of 45 minutes. In times of crises, increased follow-up frequency is usual to prevent an unnecessary hospitalization.

To enhance external validity in the study, therapists in the TAU group receive no training or supervision from the project, as they are expected to continue their clinical practice as usual. However, TAU is not “uncontrolled,” and both treatment interventions must adhere to central national guidelines. Health care within specialized treatment centers in Norway is governed by several central legislations, including The Health Personnel Act, the Patients’ Rights Act, and the Specialized Health Services Act. Furthermore, national treatment guidelines are developed regarding specific diagnosis such as attention deficit disorder, substance abuse and addiction, bipolar disorder, psychotic disorders, and depression. A central guideline that is especially relevant in this context is the National Guideline for the Prevention of Suicide in Mental Health Care in Norway [2]. This guideline is implemented in most inpatient and outpatient clinics and ensures a safety focus. According to the guideline, all patients in psychiatric care are to be asked whether they have suicidal thoughts. A formal mapping and assessment of suicidal risk by competent health workers is recommended when the patient is at risk or when he or she confirms suicidal-related problems. Generally, these guidelines describe, summarize, and recommend evidence-based treatment interventions. However, there are no fixed predefined or obligatory theoretical orientations or treatment programs demanded or expected locally or nationally.

TAU therapists in our study have diverse theoretical preferences, as the local units are not devoted to any specific orientation. Since the various theoretical orientations and supervision in TAU are unknown to the project, we will conduct a survey where this is probed. Lastly, a new initiative — a 5-year program termed “The Norwegian Patient Safety Programme: In Safe Hands” — aims to reduce patient harm and improve patient safety in Norway [41]. Suicide prevention during acute inpatient admittances is a prioritized area, and a range of measures are under continuous national implementation: The patient is to meet a specialist for assessment within 24 hours after hospitalization, rooms and surroundings at the wards are secured, and standardizing of assessment of suicidal risk at transition situations is described. Furthermore, the safety program recommends actions at the point of discharge to prevent patient harm such as developing a crisis plan, the involvement of relatives/next of kin, and the scheduling of an appointment within a week after discharge with a health professional when needed.

### Therapists’ backgrounds: CAMS and TAU

All therapists in CAMS and TAU are skilled psychologists or psychiatrists; some are specialists in their field. Thirty therapists (CAMS and TAU) are currently actively participating in the study (see Table 3). The CAMS therapist group now consists of nine adherence approved participants, where eight are psychologists and one is a psychiatrist. Four are specialists in their field of expertise and have more than 10 years of clinical experience. Among the 21 therapists in the TAU group, 6 are psychologists and 5 are psychiatrists. Further, 3 additional residential physicians participate in the TAU group. In addition, within the TAU group, an interdisciplinary team with 7 experienced nurses and social workers is part of the treatment team at sites that have acute ambulatory services. Together with a responsible psychologist or psychiatrist, this group functions as the patient’s therapist within the frame of an acute ambulatory practice. All therapists were self-selected.

**Table 3 Tab3:** Therapists’ backgrounds

	Psychologists	Doctors/residents in psychiatry	Ambulatory team- psychiatric nurse	10 years of experience or more	Specialists in clinical adult psychology	Psychiatrists/chief attending physicians
CAMS: 9	8			4	3	1
TAU: 21	6	3	7	11	3	5
SUM: 30	14	3	7	(15)	(6)	6

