### Power calculation

In calculating power, we use one-sided confidence intervals because previous studies have indicated CAMS to be superior to TAU [18, 23–25]. We use the following assumptions: (1) the main outcome variable BSSI-C score after treatment — which is scored on a 0–38 point scale — has a standard deviation of 7 points [27]; (2) there are equal sample sizes in the experimental and control groups; (3) a four-point difference in BSSI-C scores at follow-up will represent a meaningful clinical difference between CAMS and TAU; and (4) the alpha level is 0.05. Based on these assumptions, 82 % power will be achieved by including 80 participants in the trial, who will be randomized to CAMS or TAU. Assuming a 20 % drop-out rate, our desired sample size is 100 participants at inclusion.

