### Procedures to prevent treatment leakage or contamination

The project collaborates closely with the clinical units and teams participating in the trial. Leaders and clinicians are informed about the study design, purpose, and procedures as well as the importance of not contaminating the study by offering TAU participants CAMS treatment. CAMS training and supervision is offered to eligible therapists for the project only. Those who did participate at the training courses are instructed not to deliver CAMS treatment components to any patient who might be a potential participant to the trial in the future. Clinicians who have attended CAMS training and who for some reason are not participating in the project as CAMS therapists are not accepted in the TAU arm.

Furthermore, we ensure that all clinicians are informed about the trial through a system for “critical information” in the electronic patient journal system that is common to all clinical units. Each time a project participant’s journal is opened, a dialogue box appears and informs about his/her attendance in the trial and that CAMS treatment components are not to be added — especially not the SSF. Of note, three inpatient units have used the SSF as a screening tool for assessing suicidality. Two of these units are not attending the project, and the third unit has discontinued this practice before being accepted as a participating unit in the trial. Consequently, some former patients who seek treatment after a relapse may previously have been screened with the SSF. These patients are excluded and not accepted as trial participants. This is routinely controlled by the first author and one of the research assistants. Lastly, CAMS therapists may not consult patients in the TAU condition.

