### Statistical analysis

We will use generalized linear regression to examine the effects of treatment condition (CAMS versus TAU) upon suicidal thoughts (SSI-C scores) and mental health functioning (OQ-45 scores). Possible moderator effects will be estimated by using an array of covariates, including baseline measures (age, gender, ethnicity, diagnoses, and psychological measures), working alliance, medication during the treatment period, varying treatment length, new treatments delivered during follow-up, and an eventual leakage of CAMS elements into TAU.

Statistical analysis will be by intention to treat. To manage and replace missing data, we will create several sets of plausible imputed data, based on the Bayesian approach, by using multiple imputation procedures for the variables of interest, following the guidelines of Sterne and colleagues [43]. In a further sensitivity analysis we will perform the analysis using the per protocol method, excluding patients who did not complete treatment or missed measurements.

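### Therapists are nested within arm, but the 82% power assumes independent patients and the named regression has no therapist term; with any positive therapist ICC the power is overstated and the standard errors are too small

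*Protocol article*

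**What the plan says.** Under Therapists' backgrounds, the article states: "The CAMS therapist group now consists of nine adherence approved participants". It counts 21 therapists in TAU: 6 psychologists, 5 psychiatrists, 3 residential physicians and 7 nurses and social workers. The last seven work in an ambulatory team that acts as the patient's therapist jointly with a responsible psychologist or psychiatrist.

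The two groups are kept apart. Under Procedures to prevent treatment leakage or contamination, "CAMS therapists may not consult patients in the TAU condition", and clinicians who took CAMS training but are not CAMS project therapists are not accepted in TAU. Under CAMS intervention, every patient in that arm sees an approved CAMS therapist.

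The Power calculation section rests on these inputs: "we use one-sided confidence intervals because previous studies have indicated CAMS to be superior to TAU"; BSSI-C "has a standard deviation of 7 points"; "a four-point difference in BSSI-C scores at follow-up will represent a meaningful clinical difference between CAMS and TAU"; equal arms; and "the alpha level is 0.05". It concludes that 82% "power will be achieved by including 80 participants in the trial, who will be randomized to CAMS or TAU". No ICC or design effect is among the assumptions.

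The Statistical analysis section says: "We will use generalized linear regression to examine the effects of treatment condition (CAMS versus TAU) upon suicidal thoughts (SSI-C scores" and, likewise, OQ-45 scores. The covariates it goes on to list include baseline measures, working alliance, medication, treatment length, later treatments and leakage. Therapist is not among them.

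**The concern.** The treatment under test is psychotherapy, and each therapist treats patients in one arm only. Any tendency of one therapist's patients to do better or worse than another's therefore goes straight into the comparison of arms. An analysis that treats all patients as independent counts this variation as if it averaged out over 40 patients per arm, when in the CAMS arm it averages over about nine therapists.

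Two things are at stake. The stated power is a printed number that may be too high. And if the regression is run as described, its confidence intervals are too narrow whenever the therapist ICC is above zero. The article's claim in its Abstract and Discussion that similar results should follow if CAMS is adopted elsewhere extends to other therapists, so between-therapist variation belongs in the error.

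**Working it through.** **Inputs from the article.** Difference 4, SD 7, one-sided alpha 0.05, 80 analysed (40 per arm), 20% drop-out, 9 CAMS and 21 TAU therapists. **Assumed, because the article does not give them:** the therapist ICC (0.01 to 0.10), equal caseloads, and the current therapist counts holding throughout.

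**1. Reproduce the stated figure.** The SE under independence is 7 × √(2/40) = 1.565. Power = Φ(4/1.565 − 1.645) = 81.9%, which matches 82%. A two-sided test gives 72.4% and does not match. Inclusion is 80/0.80 = 100, as stated. The figure therefore corresponds to a design effect of 1.00.

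**2. Caseloads.** CAMS: 40/9 = 4.44 analysed patients per therapist. TAU: 40/21 = 1.90.

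**3. Allow for clustering.** For each arm, design effect DE = 1 + (m − 1) × ICC. Then SE = 7 × √(DE_CAMS/40 + DE_TAU/40). The power of a correctly adjusted test is Φ(4/SE − 1.645). The actual one-sided size of the unadjusted test is 1 − Φ(1.645 × 1.565/SE).

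| ICC | DE CAMS | DE TAU | SE | SE ratio | Power | One-sided size |
|---|---|---|---|---|---|---|
| 0 | 1.000 | 1.000 | 1.565 | 1.000 | 81.9% | 5.0% |
| 0.01 | 1.034 | 1.009 | 1.582 | 1.011 | 81.1% | 5.2% |
| 0.05 | 1.172 | 1.045 | 1.648 | 1.053 | 78.3% | 5.9% |
| 0.10 | 1.344 | 1.090 | 1.727 | 1.103 | 74.9% | 6.8% |

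**4. Vary the assumptions that could move the result, at ICC 0.05 and 0.10.**
- More CAMS therapists through turnover, taking 14 (the number who completed adherence training): m = 40/14 = 2.86, power 79.6% and 77.4%.
- Fewer TAU clusters because the seven nurses and social workers share care: with 21 − 7 = 14 clusters, power 77.5% and 73.5%; with 11 (psychologists and psychiatrists only), 76.9% and 72.3%.
- Uneven caseloads (assumed coefficient of variation 0.6, so m is replaced by m × 1.36), 9 and 21 therapists: power 76.5% and 71.6%, size 6.4% and 7.7%.
- Uneven caseloads and 11 TAU clusters together: power 74.7% and 68.4%, size 6.9% and 8.6%.
- A t reference on 9 + 21 − 2 = 28 degrees of freedom in the base case: power 76.5% and 73.1%, about two points below the normal approximation.

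**The case against.** **The article is a condensed account.** Random effects and variance estimators are commonly left to a full protocol or analysis plan, and neither is shown. This stands in part: a reader might infer that the final analysis will certainly ignore therapist, and the document does not establish that. It shows only a named model and a covariate list without therapist. The power statement is different, since its assumptions are listed and its figure can be reached only under independence. A later analysis plan would not correct that number.

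**The harm depends on an ICC nobody has stated.** This stands. At ICC 0.01 the loss is under one point of power and the size is 5.2%. It would be wrong to say without condition that the error rate exceeds nominal.

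**Nine is a snapshot.** This stands too. The article says therapists turn over and new ones are trained as needed. Dividing the whole sample by nine may overstate caseloads in the CAMS arm. Shared team care in TAU pulls the other way.

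**Larger error rates.** A reader might work out sizes near 10%. These need a two-sided test and an assumed strong imbalance in caseloads, whereas the article gives no caseload distribution and plans its power one-sided.

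**Self-selection.** A reader might infer that self-selected therapists differ more from one another. The article gives no basis for this. Self-selection could as well narrow the range, and in the CAMS arm a common structure and an adherence threshold may reduce variation.

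**Stratification by treatment unit** does not answer the point, because it leaves differences between therapists within a unit.

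**Conclusion.** The point holds in conditional form. Therapists are nested within arm, the 82% is an independent-patient figure, and the model as named has no therapist term. For any positive therapist ICC the standard errors are too small and the power is overstated. On the article's own one-sided basis, with equal caseloads and current therapist counts, the loss is about 1 point of power at ICC 0.01, 4 points at 0.05 and 7 points at 0.10. The size of the unadjusted test rises from 5% to 5.2%, 5.9% and 6.8%. The direction is firm given a positive ICC. The amount is not, because the ICC, the caseload spread and the final number of therapists are all unknown. This is a modest defect that is cheap to repair, not one that invalidates the trial.

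**What to change.** Record the treating therapist for each patient, or the team where an ambulatory team acts as therapist, and set a rule in advance for patients who change therapist. This is easiest while recruitment is open and data are still on paper.

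Fit the BSSI-C and OQ-45 models as linear mixed models with a therapist random intercept nested in arm and Satterthwaite or Kenward-Roger degrees of freedom. At about 1.9 analysed patients per TAU therapist, separate therapist variances by arm will be hard to estimate, so name one common variance as the fallback.

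Restate the power over a stated ICC range, such as the table above, leaving the sample size as it is.

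The cost is one extra data item, revised analysis wording, slightly wider intervals and a lower stated power. The random effect puts therapist variation into the error. It does not remove the confounding of self-selected therapists with arm, which should be acknowledged as a limit on interpretation.

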#### Removal from the trial, safety monitoring, and acceptability

All participating therapists and research assistants are health care professionals with considerable experience in the treatment and care of psychiatric patients with suicidality. With the consent of the patient, a brief report about symptom severity and diagnostic considerations obtained from the research interviews at T1 and T2 will be documented in the hospital electronic patient journal. To avoid confusion of roles and responsibility, all clinicians are reminded about their obligation to independently assess suicide risk and diagnostic assessments.

Non-responders or patients with high symptom severity (CAMS and TAU) who have been discharged from treatment at follow-up will be encouraged to contact their general practitioner for assessment and possible re-referral to treatment. Furthermore, patients with active suicidal ideation will be cared for by hospital staff or transported to an emergency room if necessary. The CAMS (or TAU) therapist is independently responsible for safety issues and will terminate CAMS (or ongoing TAU) treatment if he or she assesses the process to be insufficient or harmful. In such cases the therapist reports this information back to the research assistants. Non-responders in the TAU group are not offered subsequent CAMS treatment.

CAMS previously has been shown to be an effective treatment model [16, 17, 22]. In a pilot study from 2012, Ellis and colleagues found that CAMS was successfully implemented and accepted by both patients and clinicians within the frameworks of inpatient settings [24]. Also, in a Danish outpatient naturalistic study, CAMS was found to be feasible to implement as well as effective for reducing suicidal ideation in ordinary clinical care [25]. Patients reported that the therapeutic CAMS sessions were the essential factor for their improvement. In an online survey where adherence to CAMS treatment components was evaluated, Crowley and colleagues reported that CAMS treatment philosophy and strategies were successfully adopted, considered comfortable, and used with confidence by a large majority of 120 clinicians [42]. On this basis we expect that CAMS will probably be acceptable to the patients and clinicians within our clinic.

### Procedures to prevent treatment leakage or contamination

The project collaborates closely with the clinical units and teams participating in the trial. Leaders and clinicians are informed about the study design, purpose, and procedures as well as the importance of not contaminating the study by offering TAU participants CAMS treatment. CAMS training and supervision is offered to eligible therapists for the project only. Those who did participate at the training courses are instructed not to deliver CAMS treatment components to any patient who might be a potential participant to the trial in the future. Clinicians who have attended CAMS training and who for some reason are not participating in the project as CAMS therapists are not accepted in the TAU arm.

Furthermore, we ensure that all clinicians are informed about the trial through a system for “critical information” in the electronic patient journal system that is common to all clinical units. Each time a project participant’s journal is opened, a dialogue box appears and informs about his/her attendance in the trial and that CAMS treatment components are not to be added — especially not the SSF. Of note, three inpatient units have used the SSF as a screening tool for assessing suicidality. Two of these units are not attending the project, and the third unit has discontinued this practice before being accepted as a participating unit in the trial. Consequently, some former patients who seek treatment after a relapse may previously have been screened with the SSF. These patients are excluded and not accepted as trial participants. This is routinely controlled by the first author and one of the research assistants. Lastly, CAMS therapists may not consult patients in the TAU condition.

### Statistical analysis

We will use generalized linear regression to examine the effects of treatment condition (CAMS versus TAU) upon suicidal thoughts (SSI-C scores) and mental health functioning (OQ-45 scores). Possible moderator effects will be estimated by using an array of covariates, including baseline measures (age, gender, ethnicity, diagnoses, and psychological measures), working alliance, medication during the treatment period, varying treatment length, new treatments delivered during follow-up, and an eventual leakage of CAMS elements into TAU.

Statistical analysis will be by intention to treat. To manage and replace missing data, we will create several sets of plausible imputed data, based on the Bayesian approach, by using multiple imputation procedures for the variables of interest, following the guidelines of Sterne and colleagues [43]. In a further sensitivity analysis we will perform the analysis using the per protocol method, excluding patients who did not complete treatment or missed measurements.

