#### Aims and research questions

Our aim is to investigate whether CAMS represents improved services to patients with suicidal ideation and elevated suicidal risk in comparison to existing practices. The primary objective is to investigate whether treatment for suicidal patients by using CAMS results in a clinically and statistically significant reduction in suicidal thoughts and behaviors as compared to treatment as usual (TAU). Secondary aims are to investigate effects of CAMS and TAU upon mental health in general, symptom relief, and readmissions. Furthermore, we will test the influence of various moderating variables upon outcome, including qualities of the working alliance, the patients’ initial level of self-efficacy, and substance and alcohol abuse.

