#### Randomizing and treatment allocation

Allocation to treatment group will be performed using a stratified four-block randomization procedure with treatment unit as the stratification variable. The randomization will be concealed to the clinicians recruiting patients to the study and is carried out by an independent statistician at the Norwegian Institute of Public Health. After screening and randomizing, the study participants will be followed for one year and meet with a trained research assistant at four checkpoints: T1, T2, T3, T4 (see Fig. 1).

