#### Primary outcome

Beck’s *Scale for Suicide Ideation* - *Current (BSSI-C)* is an interview scale with 19 items that measures a patient’s suicidal ideation at its worst point during the past 2 weeks [27]. Items are scored on a Likert scale ranging from 0 to 2, where high scores indicate severe suicidal ideation. This scale has been found to be a valid and reliable measure of suicidal ideation for use with psychiatric patients, including test-retest reliability and internal consistency scores above .90 [27]. BSSI-C will be the primary inclusion measure (see above) and will be administered at baseline (T1) and at 6 and 12 months (T3, T4).

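### The primary BSSI-C comparison has no fixed time point, and the plan uses baseline measures only for moderation and does not mention the stratifying unit in the analysis

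*Protocol article*

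**What the plan says.** All references are to the protocol article.

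- **Outcome and timing.** Table 1 and the Primary outcome section make BSSI-C the sole primary outcome. It "will be administered at baseline (T1) and at 6 and 12 months (T3, T4"). No section ranks the two follow-ups or says how they are combined.
- **Sizing.** The Power calculation section assumes that the BSSI-C score following treatment "has a standard deviation of 7 points" and that "a four-point difference in BSSI-C scores at follow-up will represent a meaningful clinical difference between CAMS and TAU". It adds that "the alpha level is 0.05" and explains the direction of the test: "In calculating power, we use one-sided confidence intervals because previous studies have indicated CAMS to be superior to TAU". It sizes one comparison, with 80 analysed and 100 recruited.
- **Model.** Statistical analysis states: "We will use generalized linear regression to examine the effects of treatment condition (CAMS versus TAU) upon suicidal thoughts (SSI-C scores"). The next sentence places baseline measures in a list of covariates for possible moderator effects. The same list holds variables that arise after randomization, such as working alliance, medication, treatment length and leakage of CAMS into TAU. Baseline BSSI-C is not named; at most it falls under the general term for psychological measures.
- **Randomization.** Allocation uses a "stratified four-block randomization procedure with treatment unit as the stratification variable". Treatment unit does not appear in the analysis text.
- **Objective.** Aims and research questions asks for a "clinically and statistically significant reduction in suicidal thoughts and behaviors as compared to treatment as usual". The behaviour measures, SASIC and the registry-recorded suicide attempts, sit under secondary outcomes.

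**The concern.** A primary endpoint needs a variable and a time. Here the variable is fixed and the time is not. Describing the score as the one after treatment does not settle it, because treatment length varies by patient and no BSSI-C assessment is tied to the end of treatment. A reader of the final report could not tell from this article whether a 6-month or a 12-month difference was the one that the 80 patients were sized for. If the favourable one may be chosen afterwards, the one-sided 5% error rate no longer holds.

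The reference to behaviors in the primary objective adds to that freedom, since no behaviour measure is primary or sized.

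The second matter is smaller. BSSI-C is taken before randomization as the entry screen, so it is an ideal adjustment variable. The text gives baseline measures a different job, moderation, and mixes them with post-randomization variables. The stratifying unit is not mentioned. What is at stake there is precision, in a trial that reports recruitment difficulties.

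**Working it through.** **Inputs from the Power calculation section:** difference 4, SD 7, equal arms, one-sided alpha 0.05, 80 analysed (40 per arm), 20% drop-out.

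**Assumed, because the article gives no values:** the correlation ρ between the 6- and 12-month tests, the correlation r between baseline and follow-up BSSI-C, and the share f of outcome variance explained by unit.

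**1. The plan's own figure.**
- Standard error = 7 × √(2/40) = 1.565, and 4 / 1.565 = 2.556.
- One-sided power = Φ(2.556 − 1.645) = Φ(0.911) = 81.9%. The noncentral t with 78 degrees of freedom gives 81.3%.
- A two-sided test gives 72.4% (t: 71.4%), so the stated 82% is the one-sided figure.
- Recruitment: 80 / (1 − 0.20) = 100.

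The figure reproduces as a single, unadjusted, one-sided comparison at one time.

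**2. If both times were tested at one-sided 5% and either could count as success.** False-positive rate = 1 − Φ₂(1.645, 1.645; ρ).

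| ρ (assumed) | Rate |
|---|---|
| 0 (upper bound) | 1 − 0.95² = 9.75% |
| 0.3 | 9.3% |
| 0.5 | 8.8% |
| 0.7 | 8.0% |
| 0.9 | 6.8% |

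Splitting alpha instead (one-sided 0.025 at each time) leaves 72% power per test with 80 analysed; 82% would then need 102 analysed. Naming one contrast avoids that cost.

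**3. Adjusting for baseline BSSI-C.** Residual SD = 7 × √(1 − r²), 40 per arm, one-sided 0.05.

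| r (assumed) | Residual SD | Power, normal | Power, t | Analysed N for 82% |
|---|---|---|---|---|
| 0.2 | 6.86 | 83.2% | 82.6% | 78 |
| 0.3 | 6.68 | 84.9% | 84.4% | 74 |
| 0.4 | 6.42 | 87.4% | 86.8% | 68 |
| 0.5 | 6.06 | 90.4% | 90.0% | 62 |

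At r = 0.5 the variance falls to 1 − 0.25 = 0.75 of its raw value, and 1 / 0.75 = 1.33, so adjustment is worth one third more patients. Entry requires a score of at least 13, which narrows the baseline range and may push r toward the lower rows.

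**4. Adjusting for unit alone.** With SD = 7 × √(1 − f), power is 82.6%, 83.6% and 85.3% for f = 2%, 5% and 10%. If the stratifier is left out, the actual one-sided level is about 1 − Φ(1.645 / √(1 − f)) = 4.8%, 4.6% and 4.1%. The error is slightly conservative.

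**The case against.** The strongest reply is that this is a condensed article. The covariate set, including the stratification factor, is commonly left to an analysis plan, and one may exist. That largely stands for the adjustment part. The article excludes no covariate, and its sentence on treatment condition names the effect of interest without claiming to list the whole model. What remains is that the text does assign baseline measures a role, moderation, and that this role should be kept apart from adjustment of the primary comparison.

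The reply does not reach the time point. The article itself sets out the endpoint, the visit table, the sample size and the analysis, and together these do not identify one primary comparison.

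Several stronger readings might be inferred, and the document does not support them:

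- *The trial plans two tests at full alpha.* No section says so. The inflated rate is what the silence permits, not a stated rule.
- *The trial is underpowered because it does not adjust.* The 82% is right as calculated, and sizing on the raw SD is cautious.
- *Omitting the stratifier raises false positives.* It lowers the actual level slightly.
- *SASIC is the only behaviour outcome.* The Secondary outcomes section also includes suicide attempts from the patient registry.
- *The regression must be replaced by a repeated-measures model.* Intention-to-treat regression after multiple imputation, as planned, is an accepted method once a time is named.

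**Conclusion.** The point holds as an unfixed primary contrast, with a lesser point on adjustment. The article measures its sole primary outcome at two follow-ups, sizes one comparison and does not say which. Claiming either time at one-sided 5% would carry a false-positive rate of about 8.0% to 9.3% for assumed correlations of 0.7 to 0.3, and never more than 9.75%. This depends on both times being tested without correction, which the text permits but does not prescribe.

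The forgone precision is real but of uncertain size. Power would rise from 82% to about 83% to 90% for assumed r of 0.2 to 0.5, and unit alone would add roughly 1 to 3 points if it explains 2% to 10% of variance. Neither makes the stated sample size wrong.

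The primary objective claims more than the primary outcome can confirm, because the behaviour measures are secondary and unsized.

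**What to change.** 1. **Name one primary contrast for BSSI-C:** the arm difference at 6 months, at 12 months, or averaged over both. Make any other time secondary, or test it in a fixed order after the first succeeds. Use the same time or contrast in the Power calculation section.
2. **Adjust the primary BSSI-C model** for baseline BSSI-C and treatment unit. State this separately from the moderator analyses, and keep post-randomization variables out of the primary model. A regression after multiple imputation or a repeated-measures model would both serve.
3. **Do not carry baseline adjustment over to OQ-45 without comment.** The Recruitment section takes only BSSI-C before randomization and the remaining baseline measures after it, and patients are not blinded. Baseline OQ-45 could therefore be affected by knowledge of the arm, and any adjusted OQ-45 analysis should say so.
4. **Limit the confirmatory claim to suicidal ideation,** and report SASIC and registry suicide attempts as secondary.

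The cost is wording in the protocol, analysis plan and registry entry, with no new data and no change to the 100 patients. The downside is that, if a single time is chosen, the other gives up primary status. The change should be made and dated before outcome data are examined by arm.
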